### Statistical analysis

The data analysis will be based on an intention-to-treat approach. Baseline continuous variables will be summarized by using mean with SD or median with interquartile range as appropriate. Categorical variables will be summarized by using percentage and number of patients. The SRS will be measured repeatedly. These repeated measurements will be summarized to a mean for every patient. These values will follow a normal distribution and therefore be tested by using a Student’s *t* test. A two-sided *P* value of less than 0.05 will be considered statistically significant. The difference in SRS between the two groups will further be examined by using a general linear model. Covariates will be analyzed univariately. Covariates will be included in a multivariable analysis if the univariate *P* value is less than 0.20. A backward selection process will be used to achieve the most optimal model.

Covariates to be considered are anaesthesia- or surgery-related (for example, timing of abdominal and thoracic phase, drug dosages, use of epidural anaesthesia, and duration of surgery) and patient-related (for example, surgical history, age, weight, and body mass index). Patients with less than three surgical rating scores because of early termination of the surgical procedure will be excluded in a secondary analysis. Additional analyses will be performed on the secondary outcome parameters. No interim analysis will be done; the study will be terminated after enclosure of the last patient. Because of the amendment in sugammadex dose, the first 10 patients will be excluded for the cost analysis only. A sensitivity analysis, including the first 10 patients, will be performed.

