### Design

This study is designed as a single-center randomized controlled double-blinded trial. Patients are randomly assigned to receive either continuous infusion of rocuronium 0.6 mg/kg per hour (group 1) or continuous infusion of NaCl 0.9 % 0.06 ml/kg per hour (group 2). This is started immediately after induction. Treatment allocation will be done in a double-blinded fashion (including both the surgeon and the anaesthesiologist), to standard (on indication) versus deep NMB. Blinding will be done by a computerized randomization code. We will randomly assign according to the principle of balanced assignment: the order in which patients are classified to the different groups will be determined in a computer-randomized order. Block randomization will be done and stratified by type of surgery (start in supine or prone position) to correct for any influence of this parameter on the study endpoints. The reasons for withdrawal will be accurately documented in the case report forms. The medication is prepared and labeled by the pharmacy and supplied by the (blinded) researcher to the blinded anaesthesiologist in charge of the patient. Double blinding will be maintained during the study unless the anaesthesiologist in charge needs to unblind the data in case of a medical emergency.

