### Study procedures and measurements

Prior to the start of the study, both surgeons will be trained in rating, by practicing the SRS during two procedures, containing about 32 SRS scores. During surgery, operating conditions will be evaluated every 30 min for both the abdominal and thoracic phases by using a 5-point SRS ranging from 1 (poor surgical conditions, intervention necessary) to 5 (optimal surgical conditions) as well as a continuous numeric rating scale ranging from 1 to 100 (Table 2) [2]. Scoring will be done by the two surgeons performing the procedure ([name]). One SRS and one numeric rating score are registered each 30 min (with a variation of 31–40 min if the surgeon’s attention is needed elsewhere). If both surgeons are operating on the same patient, agreement on the score must be reached.

**Table 2 Tab2:** Surgical rating scale

1	*Extremely poor conditions*: the surgeon is unable to work because of coughing or because of the inability to obtain a visible laparoscopic field because of inadequate muscle relaxation. Additional neuromuscular blocking agents must be given
2	*Poor conditions*: there is a visible laparoscopic field, but the surgeon is severely hampered by inadequate muscle relaxation with continuous muscle contractions, movements, or both with the hazard of tissue damage. Additional neuromuscular blocking agents must be given
3	*Acceptable conditions*: there is a wide visible laparoscopic field, but muscle contractions, movements, or both occur regularly, causing some interference with the surgeon’s work. There is the need for additional neuromuscular blocking agents to prevent deterioration
4	*Good conditions*: there is a wide laparoscopic working field with sporadic muscle contractions, movements, or both. There is no immediate need for additional neuromuscular blocking agents unless there is the fear of deterioration
5	*Optimal conditions*: there is a wide visible laparoscopic working field without any movement or contractions. There is no need for additional neuromuscular blocking agents

Surgical rating scale adapted from Martini et al. [2]

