If indicated by either surgeon or anaesthesiologist, all patients, irrespective of their group assignment, can receive boluses of open-label rocuronium 0.30 mg/kg. The reason for the on-demand bolus is registered. Surgical conditions will be scored immediately before and 5 min after a bolus when requested by the surgeon only, so as not to affect blinding of the surgeons. Indications for bolus infusion are high peak inflation pressure (>35 mm Hg), high abdominal (>15 mm Hg) and thorax (>8 mm Hg) insufflation pressure, and movement, breathing, or straining of the patient. Intra-abdominal pressure will be registered every 30 min from the abdominal CO_2_ insufflation device.

For neuromuscular function monitoring, the TOF-watch SX acceleromyograph (MSD BV, Haarlem, The Netherlands) will be used. During the procedure, a TOF count (situated at the flexor hallucis brevis of the leg) will be done every 30 min at the same time as the evaluation of the surgical conditions and directly before and 5 min after an on-demand bolus [10]. Both the anaesthesiologist and the surgeon will be blinded for the results of this measurement.

When the operation is finished, a TOF count and ratio are done at the ulnar nerve (not blinded). Depth of NMB will be scored as follows: (1) very deep NMB (post-tetanic count, no twitches, (2) deep NMB (post-tetanic count, one or two twitches), (3) moderate NMB (TOF, one or two twitches), and (4) shallow or no NMB (TOF four twitches, ratio of more than 0 %). In patients with a very deep or deep NMB, a TOF is repeated 30 min after infusion of sugammadex to check for recurarization. Based on the TOF count at the end of operation, sugammadex is given at a dose of 16 mg/kg in very deep block, 4 mg/kg in deep NMB, 2 mg/kg in moderate NMB, and 2 mg/kg in shallow NMB. If recurarization is found, an additional dose of sugammadex is given on the basis of the TOF count found at that time. In case of a clinical reason to continue mechanical ventilation after surgery, administration of sugammadex is postponed until one post-tetanic twitch is found. The sugammadex dose needed in case of a very deep block (16 mg/kg) was added to the protocol after 10 patients.

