### Outcome parameters

#### Primary parameter

The primary parameter is rating of surgical conditions (SRS), as described in Table 2, during the abdominal phase of the operation [2].

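### The primary SRS mean does not separate scheduled 30-minute scores from extra scores triggered by surgeon-requested boluses

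*Protocol article*

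**What the plan says.** - **Endpoint** (Primary parameter): "The primary parameter is rating of surgical conditions (SRS), as described in Table 2, during the abdominal phase of the operation".
- **Scheduled scores** (Study procedures and measurements): "One SRS and one numeric rating score are registered each 30 min", with some slack if the surgeon is occupied.
- **Triggered scores** (same section): "Surgical conditions will be scored immediately before and 5 min after a bolus when requested by the surgeon only". Boluses requested by the anaesthesiologist add no score.
- **Who may receive boluses** (same section): "all patients, irrespective of their group assignment, can receive boluses of open-label rocuronium 0.30 mg/kg". Only group 1 has a background rocuronium infusion; group 2 has saline (Design).
- **Link between score and bolus** (Table 2): for SRS 1 and 2 the scale itself states "Additional neuromuscular blocking agents must be given". SRS 3 also describes a need for more relaxant.
- **Summary and test** (Statistical analysis): "These repeated measurements will be summarized to a mean for every patient". The per-patient means are compared with a Student's t test. The section neither limits the mean to scheduled scores nor weights by time.
- **Minimum number of scores** (Statistical analysis): "Patients with less than three surgical rating scores because of early termination of the surgical procedure" are left out of a secondary analysis. Which scores count, and in which phase, is not stated.

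**The concern.** A simple mean of scores describes a patient's average conditions if the scoring times are unrelated to those conditions. The 30-minute schedule meets that requirement. The bolus-triggered pairs do not: they exist because the surgeon, who is also the rater, judged conditions poor enough to ask for relaxant.

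If they enter the mean unweighted, each bolus adds two scores about 5 minutes apart, while the rest of the phase gets one score per 30 minutes. Group 2 has no background infusion, so more of these pairs can be expected there. That is an inference from the design and the trial's own hypothesis; the article does not say it.

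A real difference in the need for boluses is part of the treatment effect. The artefact is the extra weight on those moments. At stake is the primary comparison: two analysts following the article could obtain different primary results from the same data.

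**Working it through.** **The plan's own figure.** For a difference of 0.6, SD 0.7, two-sided alpha 0.05 and 90 % power, the normal formula gives n = 2 × (1.960 + 1.282)² × 0.7² / 0.6² = 28.6, so 29 per group. The t-test solution is 29.6, so 30 per group and 60 in total, as stated. Power at 30 per group is 90.4 %. With 10 % added, 60 × 1.10 = 66. The sample size is not in question; 0.6 and 0.7 are the yardsticks below.

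**Number of scheduled scores.** The article puts two training procedures at about 32 scores, so about 16 per procedure, or 8 per phase if the two phases are equally long. I use K = 8, and K = 6 as a lower value. The scheduled mean m, the number of surgeon-requested boluses b and the pre/post scores are **assumptions**; the article gives none of them.

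**Shift in one patient's mean.**

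Shift = (K·m + b·(pre + post)) / (K + 2b) − m = [2b / (K + 2b)] × [(pre + post)/2 − m]

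The first factor is the weight given to bolus moments. The second sets the sign: the shift is negative only if the pair averages below the scheduled mean.

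With K = 8 and b = 2 the weight is 4/12 = 33 %. The two 5-minute windows cover about 10 of 8 × 30 = 240 minutes, or 4 %.

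| Pre/post | K = 8, m = 4.0; b = 1, 2, 3 | K = 6, m = 4.1; b = 1, 2, 3 |
|---|---|---|
| 2/4 | −0.20, −0.33, −0.43 | −0.28, −0.44, −0.55 |
| 2/5 | −0.10, −0.17, −0.21 | −0.15, −0.24, −0.30 |
| 3/5 | 0.00, 0.00, 0.00 | −0.03, −0.04, −0.05 |

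Example (K = 6, m = 4.1, two boluses at 2/5): (24.6 + 14)/10 − 4.1 = −0.24, which is 40 % of 0.6. With K = 8 it is (32.8 + 14)/12 − 4.1 = −0.20. Over K = 6 to 10 and m = 4.0 to 4.4 the extreme is −0.95 (pre/post 1/4, three boluses, K = 6, m = 4.4).

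**Effect on the group comparison.** Simulation: 20,000 runs, 30 per arm, SD 0.7, K = 8, on-demand scheduled mean 4.0, Poisson bolus counts. Scheduled scores have the same distribution in both arms, and all scores enter the mean:

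| Mean boluses, on-demand v deep | 2/4: difference, rejection rate | 2/5 | 3/5 |
|---|---|---|---|
| 0 v 0 | 0.00, 5 % | 0.00, 5 % | 0.00, 5 % |
| 1 v 0.2 | 0.13, 12 % | 0.07, 7 % | 0.00, 5 % |
| 2 v 0.3 | 0.24, 33 % | 0.12, 12 % | 0.00, 5 % |
| 3 v 0.5 | 0.30, 53 % | 0.15, 18 % | 0.00, 5 % |

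With a true difference of 0.6 in the scheduled scores and 2 v 0.3 boluses, the observed difference is 0.81 (2/4), 0.69 (2/5) and 0.57 (3/5). The last is slightly too small, so the error can run against deep block.

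**Scheduled scores only.** The triggered scores then have no influence. Rejection is about 5 % with no difference and about 90 % at 0.6.

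**The case against.** **The article never says that triggered scores enter the mean.** This stands. The scheduled series is the nearest description of the repeated measurements, and the article's count fits it: an operation of about 8 hours scored every 30 minutes gives 16 scores, so 32 for two procedures with no bolus scores. But that count describes rater training, not the analysis, and the averaging sentence excludes nothing. The finding is therefore an unseparated rule, not a documented inclusion.

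**It is an analysis-plan detail.** Partly so: the analysis plan is not shown and may settle it. Still, the article itself sets two sampling schemes for one scale and one averaging rule over both. Which scores make up the primary endpoint is close to protocol content.

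**The post-bolus score offsets the pre-bolus score.** This stands. At 3/5 the shift is about zero. A surgeon who expects the requested bolus to work may score it higher, which would narrow the gap between arms. Boluses are open-label in both arms, so knowing of one does not reveal allocation. A reader might infer that the rule always favours deep block; the arithmetic does not support that.

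**Type I error.** A reader might take the 12 % to 53 % rejection rates as the trial's type I error. They are not. If treatment affects nothing, bolus counts are equal on average in both arms and the test is not inflated. These rates need equal scheduled scores together with unequal bolus counts. That is possible if rescue restores conditions between scheduled times, but it is one scenario.

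**Scheduled scores alone may miss poor episodes** rescued between time points. This also stands, and it is the reason for the sensitivity analysis.

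**Conclusion.** The concern holds as a defect in how the primary summary is specified. The averaging rule covers all repeated SRS measurements and does not separate scheduled scores from those triggered by surgeon-requested boluses. Read literally, it over-weights outcome-triggered moments, probably more in the on-demand arm.

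With 6 to 8 scheduled scores averaging 4.0 to 4.1 and one to three boluses, a patient's mean shifts by about 0 (3/5) to about −0.5 (2/4, three boluses), against a planned difference of 0.6. The number of scheduled scores is inferred from the training count; their mean, the bolus counts and the bolus scores are assumed. Size and sign are thus unknown in advance, which is why the rule has to be settled in advance.

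A reader might also infer that the minimum-of-three-scores rule distorts the primary result. It does not: it governs only a secondary analysis, though it shares the ambiguity about which scores and which phase count.

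This should be fixed. Confidence is moderate, because the article leaves inclusion open and an analysis plan not shown may resolve it.

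**What to change.** - Define the primary endpoint as the per-patient mean of the scheduled 30-minute SRS scores in the abdominal phase.
- Report the pre- and post-bolus scores separately and descriptively.
- Add a time-weighted mean of all abdominal-phase scores as a sensitivity analysis.
- Apply the minimum-of-three rule of the secondary analysis to scheduled abdominal-phase scores.
- Settle this before unblinding.

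**Cost.** A few sentences of wording and a scheduled/unscheduled flag on each score. No new data are needed and the sample size is unchanged. The small downside is that poor episodes rescued between scheduled times appear only in the bolus outcomes, which are already secondary parameters, and in the sensitivity analysis.

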## Discussion

This study is the first to evaluate the benefits of deep neuromuscular relaxation during thoracolapascopic esophageal surgery. In addition, this type of surgery is unique in that it consists of both an abdominal and a thoracic phase and because of its long duration, enabling acquisition of an adequate number of SRS scores. Considering the results of earlier studies, we can expect a benefit in operating conditions of deep neuromuscular relaxation during the abdominal phase. However, whether the operation is started with the abdominal or thoracic phase may influence SRS scores because of cumulative doses of anaesthetics in a later phase. Therefore, the benefit may be smaller when the abdominal phase comes last. To better determine this influence, patients are randomly assigned in blocks. Whether a benefit can be found during the thoracoscopic phase has yet to be determined. The ribcage will keep the surgical field open, and the diaphragm may be the only influence on surgical conditions. In addition, as this operation normally takes 8 h, deep neuromuscular relaxation may shorten duration of operation. However, this benefit may be counteracted by the costs of rocuronium and sugammadex and time until extubation. A cost analysis will be done to answer this question.

We will use the same scoring system as was developed by Martini et al. [2]. It showed adequate reliability in discrimination between surgical conditions and a low variability between surgeons. The scoring will be performed by two surgeons with ample experience with the procedure, and both are trained in SRS scoring before the start of the study. In contrast to Martini et al., we chose not to include the anaesthesiologist in the SRS scoring, because of lack of expertise in assessing the quality of the (laparoscopic/thoracoscopic) surgical field. Anaesthesiologists will assess the anaesthesia conditions (peak and mean respiratory pressures, incidence peak insufflation pressure of more than 35 mm Hg, depth of NBM at the end of surgery, intraoperative cardiac and respiratory incidents, and the indication for on-demand neuromuscular blocking agent).

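### Randomisation is stratified by starting position, but the primary t test omits the stratum and the secondary model keeps it only if a P-value rule allows; the cost is a conservative, less precise test, not bias

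*Protocol article*

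**What the plan says.** The Design section of the protocol article states that block randomisation is "stratified by type of surgery (start in supine or prone position) to correct for any influence of this parameter on the study endpoints".

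The endpoint is fixed under Primary parameter: "The primary parameter is rating of surgical conditions (SRS), as described in Table 2, during the abdominal phase of the operation". The Statistical analysis section then reduces the repeated scores: "These repeated measurements will be summarized to a mean for every patient". Of these means it says "These values will follow a normal distribution and therefore be tested by using a" Student t test. No stratum term is named for that test.

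A second step follows: "The difference in SRS between the two groups will further be examined by using a general linear model". Phase order appears here, among the candidates: "Covariates to be considered are anaesthesia- or surgery-related (for example, timing of abdominal and thoracic phase, drug dosages" and others. Entry is conditional: "Covariates will be included in a multivariable analysis if the univariate" P value is below 0.20, after which backward selection is applied.

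The Discussion expects the gain from deep block to be possibly smaller when the abdominal phase comes last, and adds: "To better determine this influence, patients are randomly assigned in blocks".

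**The concern.** A factor important enough to stratify on is normally carried into the primary analysis. Stratified allocation makes the two arms more alike than simple randomisation would. An ordinary two-sample t test does not know this: it leaves the variation between supine-start and prone-start patients in its error term. If phase order affects SRS, the standard error is then too large, the confidence interval too wide and the real type I error below 5%.

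The follow-on model does not settle the matter, because it comes after the primary test and whether it contains phase order depends on the data. A design factor should not have to earn its place through a significance screen.

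There is also a smaller gap. The Discussion anticipates that the benefit may vary with phase order. Estimating that needs treatment differences within each stratum or a treatment-by-stratum term. A main-effect covariate gives neither, and allocation in blocks estimates nothing by itself.

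**Working it through.** **Inputs from the protocol article.** Sample size calculation: difference 0.6, SD 0.7, two-sided alpha 0.05, 90% power, 60 patients in total. Allocation is taken as 1:1, from the balanced-assignment wording and the per-group sample size table.

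**Inputs that are assumptions.** The document gives neither the size of the stratum effect nor the split between strata. I take a supine/prone difference g of 0 to 1.0 SRS points, equal strata, exact 1:1 balance within each stratum, and a total SD of 0.7 that includes the stratum effect.

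**1. The plan's own figure.** The noncentral-t calculation gives 30 per group with power 0.904, and all 12 cells of Table 3 reproduce. The stated 60 is therefore right for an unadjusted t test.

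**2. Formulas.** With equal strata the stratum explains R² = 0.25 g² / 0.7² of the variance. The t test's standard error is then too large by a factor of about 1/√(1 − R²). For g = 0.3: R² = 0.0225/0.49 = 4.6%, factor 1.02. For g = 0.7: R² = 0.1225/0.49 = 25%, factor 1.15.

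**3. Simulation.** 20,000 trials of 60 patients per scenario, comparing the t test with a linear model on treatment and stratum (adjusted). Power and the screen are at a treatment difference of 0.6, the same in both strata.

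| g (SRS points) | R² | Type I, t test | Type I, adjusted | Power, t test | Power, adjusted | Stratum passes P<0.20 screen |
|---|---|---|---|---|---|---|
| 0 | 0% | 4.9% | 4.9% | 90.4% | 90.3% | 16% |
| 0.3 | 4.6% | 4.2% | 4.7% | 90.7% | 91.5% | 61% |
| 0.5 | 12.8% | 3.4% | 4.7% | 91.8% | 93.9% | 94% |
| 0.7 | 25% | 2.3% | 5.0% | 92.8% | 96.3% | 99.8% |
| 1.0 | 51% | 0.5% | 5.1% | 96.4% | 99.6% | 100% |

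At R² = 20% (g about 0.63) the t test has type I error of about 2.8%, and power is 92.6% against 95.4% adjusted. A 70:30 split gives similar results: t-test type I error of 4.5%, 3.8% and 2.7% at g = 0.3, 0.5 and 0.7.

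**4. If the benefit itself differs by stratum.** With g = 0.3, an average benefit of 0.6, and benefits that differ by 0.3 or 0.6 points between strata, power is 89.7% or 87.6% for the t test and 91.5% or 91.0% adjusted. In these runs the SD in the treated arm exceeds 0.7: √(0.4675 + 0.25 × 0.6²) = 0.75 and √(0.4675 + 0.25 × 0.9²) = 0.82. They therefore lie outside the planning assumption and show no shortfall against it.

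**5. Precision of an interaction estimate.** With 15 patients per cell, SE = 0.7 × √(4/15) = 0.36, so the 95% half-width is about 2 × 0.36 = 0.7 points. Simulated power of the interaction test is about 13% for a 0.3-point and 38% for a 0.6-point difference in benefit.

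**The case against.** The case against is substantial. Stratified blocks already balance starting position between the arms, which removes it as a confounder. A reader might infer that the promised correction is not made at all, but the documents do not support that: allocation does part of the work, and the secondary model lists phase timing as a candidate.

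The screen also seldom drops a factor that matters. At g = 0.5 it passes in 94% of trials. It is often lost at g = 0.3, where adjustment gains only about 1 point of power. This defence is incomplete, because no backward-selection threshold is printed and final retention cannot be calculated.

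The larger losses need a large stratum effect. An R² of 20% means a shift of about 0.63 points, more than the treatment difference the trial is powered for, and the document says only that order may influence scores.

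A reader might also infer that the question about phase order cannot be answered. That is too strong. The Discussion's wording can be read as the main effect of order on SRS, and the planned univariate analysis of covariates would estimate that if timing is considered as listed. Only the effect of order on the benefit has no stated analysis. It is an expectation in the Discussion, not a listed endpoint, and such an analysis is often left to a statistical analysis plan, which is not at hand.

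What stands is narrower: the primary test is fixed in the document, it omits the stratum, and nothing guarantees the stratum a place in the secondary model.

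**Conclusion.** The point holds as a matter of efficiency and of consistency between design and analysis. The treatment estimate is unbiased and the false-positive rate is not inflated. The stated 90% power at a difference of 0.6 is met in every scenario with a common benefit and a total SD of 0.7. Reading the t test as invalid or the trial as underpowered on this ground would be wrong.

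The cost is a conservative test and some lost precision. A stratum difference of about 0.3 points gives a type I error of about 4% and about 1 point of power forgone. A difference of 0.6 to 0.7 points gives 2 to 3% and about 3 points. These sizes rest on assumed stratum effects and an assumed equal split. If phase order has no effect on SRS, nothing is lost.

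**What to change.** Make the primary analysis a linear model of each patient's mean abdominal SRS on treatment and type of surgery (two- or three-stage, that is, supine or prone start). Retain the stratum whatever its P value, and keep the t test as a supportive analysis. Exempt the stratum from the univariate screen and from backward selection in the further model.

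Optionally, because a smaller benefit is expected when the abdominal phase comes last, report the treatment difference within each stratum and the treatment-by-stratum interaction with its 95% confidence interval. Label these as exploratory and state beforehand that the interval will be wide, about 0.7 points either side.

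The primary change costs one sentence and one degree of freedom, and leaves the sample size as it is. It should be fixed before unblinding, so that nobody chooses between the t test and a selected model after seeing the results.

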#### Secondary parameters

Rating of SRS during thoracic phase of the operation, number of on-demand boluses infused, and indication of on-demand bolus administration.Rating of anaesthesia conditions, including peak and mean respiratory pressures and incidence peak insufflation pressure of more than 35 mm Hg; depth of NBM at the end of surgery, intraoperative cardiac and respiratory incidents; and time until spontaneous breathing and time until extubation after interruption of sedation.Costs: amount of rocuronium used (milligrams), dose of sugammadex needed (milligrams) to reach a TOF of more than 90 %, time to reversal, number of patients (percentage) with recurarization measured 30 min after reversal and consequently the need for additional sugammadex, and duration of surgery and operating room occupancy (expressed in hours and personnel cost per hour) and ICU stay.Perioperative surgical complications.The ability of surgeons and anaesthesiologists to estimate post-operatively to which group the patient was randomly assigned (at the end of each of the two phases).

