### Sample size calculation

The sample size is based on an article by Martini et al. [2], who showed a difference of 0.7 points on the SRS and a standard deviation (SD) of 0.4. However, compared with the retroperitoneal surgery studied in that article, the current procedure of esophagectomy is anticipated to have more sources of variability for the surgical conditions. This may reduce the benefit or effect size of treatment to some degree but in particular will increase the variability, even when adjusting for body mass index and the presence of previous procedures, as other factors cannot be effectively controlled. Table 3 shows a range of plausible effect sizes and (adjusted) SDs of the SRS. A sample size of 60 in total would provide a power of 90 % to show a mean difference of 0.6 with a standard deviation of 0.7 and a two sided alpha level of 0.05. This mean difference is slightly lower than observed in the study by Martini et al of 0.6 points on the SRS and a somewhat increased SD of 0.7 points on the SRS. A drop-out of 10 % is expected and therefore we will include 66 patients. After withdrawal of informed consent before the operation but after randomization, the subject will be replaced by a new patient.

**Table 3 Tab3:** Range of plausible effect sizes and (adjusted) standard deviations of the SRS

Mean group difference	Standard deviation			
	0.5	0.6	0.7	0.8
0.5	23	32	43	55
0.6	16	23	30	39
0.7	12	17	23	29

Sample size per group by a range of mean group differences and standard deviations (SDs) on the surgical rating scale (SRS) at 90 % power. A sample size of 60 in total would provide a power of 90 % in case the effect size is slightly lower as observed in Martini et al. [2] of 0.6 points on the SRS and a somewhat increased SD of 0.7 points on the SRS. A drop-out of 10 % is expected and therefore we will include 66 patients

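### The supporting linear model for the SRS may adjust for duration of surgery and drug dosages, which treatment or the SRS itself can change; the primary t test is unaffected

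*Protocol article*

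**What the plan says.** All of this is in the Statistical analysis section of the protocol article unless another section is named.

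- The analysis follows intention to treat. Repeated SRS scores are averaged per patient: "These values will follow a normal distribution and therefore be tested by using a Student’s *t* test". The criterion is: "A two-sided *P* value of less than 0.05 will be considered statistically significant".
- The SRS difference is then examined further in a general linear model. Covariates enter if their univariate P value is below 0.20, and then: "A backward selection process will be used to achieve the most optimal model". No retention threshold is given.
- The anaesthesia- and surgery-related candidates, given as examples, are "timing of abdominal and thoracic phase, drug dosages, use of epidural anaesthesia, and duration of surgery". Patient-related examples are surgical history, age, weight and BMI.
- Under Secondary parameters, the cost outcomes include "amount of rocuronium used (milligrams") and duration of surgery.
- The Discussion expects that "deep neuromuscular relaxation may shorten duration of operation".

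**The concern.** The linear model is there to estimate the treatment difference in the primary parameter. Covariates in such a model should be fixed before treatment can act on them. Two of the named candidates are not:

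- **Rocuronium dose** is set by the randomised infusion (Design). It also rises when conditions are poor: the two lowest SRS grades require more blocking agent (Table 2), and movement or straining is an indication for an open-label bolus (Study procedures and measurements).
- **Duration of surgery** is expected by the protocol itself to respond to deep block.

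Conditioning on either one changes the question. The arm coefficient no longer compares the groups as randomised. The trial could then report two different effects on its primary parameter, one of them an artefact of adjustment.

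**Working it through.** **1. The plan's own figure.** The Sample size calculation claims 90% power from 30 patients per group (60 in all), for a 0.6-point difference, SD 0.7 and alpha 0.05 two-sided. With 30 per group the standard error is 0.7 × √(2/30) = 0.181, the noncentrality is 0.6/0.181 = 3.32 and df = 58. The noncentral t gives power 90.4%, and 30 is the smallest group size that reaches 90%. The figure reproduces for the unadjusted t test.

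**2. How far treatment sets the dose.** Infusion 0.6 mg/kg per hour (Design) × about 8 h (Discussion) = 4.8 mg/kg, in group 1 only. Induction at 1.0 mg/kg and boluses of 0.30 mg/kg apply to both groups. Total dose is therefore close to a relabelling of the arm, plus a part that can rise when SRS is poor.

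**3. Duration as the only candidate.** Assume duration = 8 − k × SRS + noise with SD 1 h, where SRS has within-group SD 0.7. Regressing SRS on arm and duration multiplies the arm coefficient by 1/(1 + 0.49k²):

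| k (h per SRS point) | factor | true 0.6 becomes |
|---|---|---|
| 0.25 | 1/1.0306 = 0.970 | 0.58 |
| 0.5 | 1/1.1225 = 0.891 | 0.53 |
| 1.0 | 1/1.49 = 0.671 | 0.40 |

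A simulation of the selection rule (4,000 replicates, 30 per arm, entry P < 0.20, retention P < 0.05 assumed) gave mean estimates of 0.59, 0.54 and 0.40, with power 89%, 87% and 73%. The t test had about 90%. With no true effect, type I error was 5.6%, 5.4% and 4.6%: a multiple of zero is still zero.

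**4. Rocuronium dose as a candidate as well.** The assumptions are:
- total dose = 1.0 + 0.6 × duration × arm + 0.30 × boluses;
- about 2 boluses at average control-group SRS, falling as SRS rises (Poisson mean 2·exp(−b·SRS), with SRS centred on the control mean);
- duration as in step 3, with the k shown;
- five unrelated baseline covariates also offered;
- 2,500 replicates under the same selection rule.

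| b, k | no effect: mean estimate | type I error | true 0.6: mean estimate |
|---|---|---|---|
| 0, 0 | −0.01 | 6.2% | 0.60 |
| 0.3, 0.3 | 0.34 | 17% | 1.48 |
| 0.6, 0.5 | 1.07 | 45% | 2.11 |
| 1.0, 0.5 | 1.78 | 76% | 1.74 |

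The t test stayed at about 5% type I error. A variant with a different noise structure (residual SD 1 for boluses and hours; centre case 1 bolus and 0.5 h per SRS point) gave 15%, 41% and 64% from weak to strong dependence. Together the range with dependence is 15–76%.

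**5. Why the bias runs upward here.** Within an arm, more boluses go with worse SRS, so the dose slope is negative. The infusion adds 4.8 mg/kg to group 1. With no true effect, the model offsets that predicted loss with a positive arm coefficient of 4.8 × |slope|. With both variables forced in and the weak dependence (0.3, 0.3), the mean coefficient was 1.40, which implies a slope of −1.40/4.8 = −0.29 points per mg/kg.

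**6. Selection among baseline covariates only.** With 5 to 8 candidates, type I error was 5.0–5.9%, and a true 0.6 was estimated as 0.593.

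**The case against.** - **The primary result is safe.** This stands. The t test comes first, the sample size reproduces for it, and the model only supplements it. A reader might infer that the trial's main conclusion is at risk; the document does not support that.
- **Drug dosages does not name rocuronium, and the list is only by way of example.** This stands in part. The Discussion mentions cumulative anaesthetic doses, so sufentanil or sevoflurane may be meant. But nothing excludes rocuronium, the drug under study, and duration is explicit.
- **Far larger harm can be computed.** Forcing total rocuronium into the model with no true effect gives about 2.8 points and rejection in about 99% of trials. The plan does not force it in: a covariate must pass the screen and survive backward selection, and the lower range in steps 3 and 4 applies.
- **Adjustment removes part of a real effect.** This cannot be said without conditions. Duration pulled the estimate down and total dose pushed it up. The document does not fix the direction.
- **P-value selection by itself makes the P value invalid.** A reader might infer this, but with baseline covariates the loss is at most about one percentage point, near simulation error (about 0.4 points at 2,500 replicates). It is a side remark.

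**Conclusion.** The point holds, limited to the supporting model: should fix. As written, the linear model may condition on variables that the randomised treatment or the SRS can change and that the protocol itself lists as outcomes. The adjusted effect would then not be the intention-to-treat effect.

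The explicit part, duration, leaves type I error near 5% and costs between almost nothing and a third of the effect. The conditional part, rocuronium dose, is the serious one if drug dosages covers it. If boluses and duration do not depend on SRS, selection does little harm (6.2%). Table 2 makes some dependence likely, but its strength is not stated. All sizes rest on the assumed dependence and on the assumed 0.05 retention level.

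**What to change.** In the Statistical analysis section:

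1. Remove drug dosages, duration of surgery and any other variable arising after randomisation from every model that estimates the treatment effect.
2. Replace the screen and backward selection with one pre-specified model for mean SRS: treatment, type of surgery (the stratification factor), BMI and previous surgery, with no term dropped. The Sample size calculation already names the last two as adjusters.
3. Label any model that contains dose or duration as descriptive, and do not report its arm coefficient as a treatment effect.

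This changes wording only. It needs no new data, and the sample size and the t test stay as they are.
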